### Additional consent provisions for collection and use of participant data and biological specimens {26b}

On the consent form, participants will be asked if they agree to use of their data should they choose to withdraw from the trial. Participants will also be asked for permission for the research team to share relevant data with people from the universities taking part in the research or from regulatory authorities, where relevant. This trial does not involve collecting biological specimens for storage.

## Interventions

### Explanation for the choice of comparators {6b}

The comparator is routine care as per “Iturrama Primary Care” procedures informed by the WHO international practice guidelines [13].

### Intervention descriptions {11a}

Participants will be randomly assigned in a 1:1 ratio to one of two groups: the exercise group and the routine care group. The exercise group will undergo a 12-week exercise intervention, followed by a 12-week follow-up period. On the other hand, the routine care group will undergo a 12-week period of routine care, followed by a 12-week follow-up period. If participants are not engaging 2 times per week, the research team will reach out through email and/or phone to get a clear explanation as to why and to motivate the participants to continue. If the participants do not perform 70% of the training (or 17 out of 24 sessions), they will not be allowed to continue participation. The overall study procedure is illustrated in Fig. 1.

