### Eligibility criteria {10} and recruitment {15}

A total of 80 children of both sexes between the ages of 4 to 5 years old will be recruited from the “Iturrama Primary Care” (Pamplona, Navarra, Spain). Participants will be admitted if their parent(s)/guardian(s) have provided informed consent for their participation in the project and if, according to their pediatrician, they do not have physical or mental disorders that would prevent them from completing the assessment tests or participating in the exercises provided in the intervention program. It is a requirement to have at least one parent/guardian answer the questionnaires included in the protocol. Participants (children) who at the start of the project present a psychiatric disorder or chronic illness that limits their participation in physical activities, those who do not comply with the established procedures, and those who do not understand the Spanish language will be excluded from the study.

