### Exercise group

If allocated to the intervention group, participants will undergo a 12-week exercise intervention utilizing a gamified online platform designed for children to engage in physical activity with their families at home or in outdoor spaces (Fig. 2), followed by a 12-week follow-up period. The platform features pre-recorded video exercises and is designed to be followed by normal daily routines. Participants are required to log in and complete the exercises 2 times per week, with a different session available Monday to Wednesday and repeated from Thursday to Sunday. The program consists of various phases, including bodyweight strength training, cardiovascular exercises, and color-coded exercises, with varying exercises and repetition counts or duration from week to week. Each session includes a warm-up/activation phase, a training phase, and a cool down phase. The warm-up phase is 3 min of light intensity continuous training, the training phase is 10–26 min with 6–12 repetitions, 20–40 s of work, and 10–20 s of recovery, and the cool down phase is 3 min of static and dynamic exercises. The exercises will change each week, increasing in length and intensity. The program will be supervised by the child’s parent(s) or guardian(s).

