### Routine care group

Participants allocated to the control group will continue to receive routine care according to WHO international practice guidelines [13], followed by a 12-week follow-up period. These activities include engaging in physical education class at school and/or playing with friends at the park or in the backyard. To ensure adherence to the intervention, the research team will closely monitor participant engagement, reaching out to participants who are not logging in twice per week to understand the reasons for non-compliance and to provide motivation to continue. Participants who do not execute their training will not be allowed to continue with the study.

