## Statistical methods

### Statistical methods for primary and secondary outcomes {20a}

The study will adhere to the intention-to-treat principle and use the baseline observation carried forward imputation method, where missing data will be replaced by baseline values [39]. The final analysis population will be described and any differences from the enrolled population will be reported. Participants who drop out of the study may still be included in the analysis, although their data will provide less information and lower the estimated effects variance. Adherence will be measured as the number of completed sessions divided by the total number of sessions, expressed as a percentage. The first step of the analysis will be to calculate descriptive statistics for the overall sample and between groups. Since this is an experimental design with primary and secondary outcomes measured at three timepoints - baseline (t0 = week 0), post-intervention (t1 = week 12), and after a 12-week follow-up period (t2 = week 24) - for the two study groups (exercise and routine care), a comparative analysis between the measurements will determine the differences. A linear mixed model with repeated observations will be used for these comparisons, when appropriate, for each dependent variable. Subsequently, multivariate analysis will be carried out, and the autocorrelation between repeated measures will be taken into account. We will use longitudinal analysis methods, such as a generalized estimating equation approach, to control the differences among measurements at baseline and to incorporate incomplete observations into this analysis. Pearson correlations will be calculated between the maximal values of the primary and secondary outcomes. All analyses will be 2-sided and a significance level of *α* ≤ 0.05 will be used for the primary analysis.

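### Ending study participation below 17 of 24 sessions is a one-arm, adherence-based removal after randomisation that conflicts with the stated intention-to-treat principle

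*Protocol article*

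**What the plan says.** Intervention descriptions {11a} sets the rule: "If the participants do not perform 70% of the training (or 17 out of 24 sessions), they will not be allowed to continue participation". The sessions belong to the exercise group alone. Its section says "Participants are required to log in and complete the exercises 2 times per week", for 12 weeks. For the other arm the text is "Participants allocated to the control group will continue to receive routine care according to WHO international practice guidelines", with school physical education and free play as examples.

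The Routine care group section nevertheless goes on to describe contacting families who do not log in twice a week, and ends: "Participants who do not execute their training will not be allowed to continue with the study". That sentence makes the consequence departure from the study, not only from the exercise sessions.

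Statistical methods {20a} says: "The study will adhere to the intention-to-treat principle and use the baseline observation carried forward imputation method". It adds "Participants who drop out of the study may still be included in the analysis", and allows the final analysis population to differ from the enrolled one provided that the difference is reported. Section {20c} adds sensitivity analyses for missing data. Section {26b} asks for consent to use the data of those who choose to withdraw. No section says whether a child removed for low adherence is still assessed at T1 (week 12) or T2 (week 24).

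**The concern.** Intention-to-treat requires that outcomes be sought from every randomised child, whatever the number of sessions completed. Here the protocol itself ends participation on the basis of adherence. Because only one arm can fail the rule, any resulting loss of outcomes is one-sided. It also selects on family motivation for physical activity, which is plausibly related to the primary outcome, mean daily minutes of MVPA. If removed children drop out of the analysis, the more adherent part of the exercise arm is compared with all controls, and randomisation no longer protects that contrast. If they stay in with baseline values, those values replace outcomes that the rule may have prevented from being measured.

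**Working it through.** **The threshold.** 2 sessions × 12 weeks = 24. 0.70 × 24 = 16.8, rounded up to 17 (17/24 = 70.8%; 16/24 = 66.7%). The protocol's figure reproduces.

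**When a child can fail.** After 8 missed sessions at most 16 remain possible, so the threshold is out of reach. At 2 per week this can happen by the end of week 4, before both T1 and T2. The protocol does not say when the count is applied. Applied at week 12, it would still precede T2.

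**Illustration 1: removed children are left out.** The protocol gives neither an SD for MVPA nor an expected rate of low adherence, so these are assumptions:
- fraction removed, f = 0.10, 0.20 or 0.30;
- removed children's MVPA 0.5 SD below that of the others;
- SD of 7.7 or 20 min/day. The first is back-solved from the stated 5-minute difference, two-sided alpha 0.05, power 0.80 and 37 to 38 evaluable per group: SD = 5 / [(1.96 + 0.84) × √(2/n)] = 7.7 to 7.8. The second is a plain assumption.

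Full-arm mean = adherers' mean − f × 0.5 SD, so exclusion shifts the exercise mean by +0.5f SD.

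| f | Shift (SD) | SD 7.7 (min/day) | SD 20 (min/day) |
|---|---|---|---|
| 0.10 | 0.05 | 0.4 | 1.0 |
| 0.20 | 0.10 | 0.8 | 2.0 |
| 0.30 | 0.15 | 1.2 | 3.0 |

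The protocol's target difference is 5 min/day.

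**Illustration 2: exclusion against baseline carried forward.** A simulation of change from baseline assumed no true effect, an SD of change of 7.78, a correlation of 0.3 between adherence and change, and removal of the lowest adherers.
- Exclusion at 10/20/30% removed gives a spurious difference of about +0.45/+0.8/+1.2 min/day. With 40 per arm randomised, two-sided type I error is about 5.8/7.3/9.3%.
- Baseline carried forward at 20% removed gives about +0.7 with no time trend, −0.35 with a trend of +5 min/day, and +1.7 with a trend of −5.

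The last result can be checked by hand. The lowest 20% on adherence have a mean change 0.3 × 1.40 × 7.78 = 3.27 below average. Setting their change to zero alters the arm difference by 0.20 × (3.27 − trend): +0.65, −0.35 and +1.65 for trends of 0, +5 and −5. The sign therefore depends on a trend that the protocol does not give.

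**The case against.** The strongest defence is that leaving the study is not the same as leaving the analysis. Baseline carried forward can keep every randomised child in the allocated arm, {26b} seeks consent to use data after withdrawal, and {20c} adds multiple imputation and nonignorable models. This stands against one tempting inference, that the rule and intention-to-treat can never coexist. It does not settle the conflict. The inclusion of dropouts is permissive, {26b} concerns families who choose to withdraw, and the sensitivity analyses explore missing data without preventing it.

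Other stronger readings also go beyond the text:
- *Removed children's outcomes are never measured.* The protocol is silent on this, and the timing of removal is unstated.
- *Every comparison is biased.* There is no bias from this rule if nobody is removed. Planned control for baseline differences could also absorb part of a gap in MVPA level, so Illustration 1 may overstate the shift in an adjusted analysis.
- *Carrying baseline forward costs a definite amount of power.* That charges the rule with dilution that full follow-up might show too. If low adherers gain nothing, following them all gives the same diluted mean.
- *The eligibility section removes randomised children.* The phrase "those who do not comply with the established procedures" stands in a list of exclusions headed by conditions present at the start, and mentions neither sessions nor adherence. It is ambiguous, no more.
- *Controls will be removed or made to train.* Read literally, the routine care section says so, but that arm has no platform sessions, so misplaced text is the likelier explanation.

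**Conclusion.** The concern holds as a conflict that needs resolving before the analysis. Two sections end study participation for low adherence, the rule can act only in the exercise arm, and the statistical section states "The study will adhere to the intention-to-treat principle" without committing to follow or analyse the removed children. If any child is removed, every post-baseline between-group comparison is at risk of bias. Under exclusion the bias favours exercise, provided that low adherers tend to have lower MVPA. Under baseline carried forward its direction is uncertain. The range of 0.05 to 0.15 SD rests wholly on the assumed 10% to 30% removal and the 0.5 SD gap, and the minutes also on the assumed SD. These figures show that the problem could matter against a 5-minute target; they are not a forecast.

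**What to change.** Reconcile {11a}, the Routine care group section and {20a} as follows:
- State that low adherence does not end study follow-up, and that all randomised children are invited to T1 and T2 and analysed in the arm allocated.
- Use 17 of 24 sessions only to define a supportive per-protocol set.
- Remove the log-in and training sentences from the routine care section.
- Clarify that the exclusion for not complying with procedures, in the eligibility section, applies only before randomisation.

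Whether a child keeps access to the platform is a separate matter for the investigators.

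The cost is a wording amendment and assessment visits for enrolled children who would otherwise have left. At an assumed 10% to 30% of 40 this is 4 to 12 children. Recruitment began in November 2022, so outcomes already missed cannot be recovered; any such children should be reported by arm with the reason for removal.

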**Fig. 1 Fig1:**
[figure not shown]
Flow of subjects through the “3, 2, 1 Move on Study.” Participants will be first randomly assigned to a 12-week period of standard daily routines (*n* = 40) or exercise training (*n* = 40). Both groups will be included in a 12-week follow-up period

### Exercise group

If allocated to the intervention group, participants will undergo a 12-week exercise intervention utilizing a gamified online platform designed for children to engage in physical activity with their families at home or in outdoor spaces (Fig. 2), followed by a 12-week follow-up period. The platform features pre-recorded video exercises and is designed to be followed by normal daily routines. Participants are required to log in and complete the exercises 2 times per week, with a different session available Monday to Wednesday and repeated from Thursday to Sunday. The program consists of various phases, including bodyweight strength training, cardiovascular exercises, and color-coded exercises, with varying exercises and repetition counts or duration from week to week. Each session includes a warm-up/activation phase, a training phase, and a cool down phase. The warm-up phase is 3 min of light intensity continuous training, the training phase is 10–26 min with 6–12 repetitions, 20–40 s of work, and 10–20 s of recovery, and the cool down phase is 3 min of static and dynamic exercises. The exercises will change each week, increasing in length and intensity. The program will be supervised by the child’s parent(s) or guardian(s).

**Fig. 2 Fig2:**
[figure not shown]
Example of gamified online platform

### Routine care group

Participants allocated to the control group will continue to receive routine care according to WHO international practice guidelines [13], followed by a 12-week follow-up period. These activities include engaging in physical education class at school and/or playing with friends at the park or in the backyard. To ensure adherence to the intervention, the research team will closely monitor participant engagement, reaching out to participants who are not logging in twice per week to understand the reasons for non-compliance and to provide motivation to continue. Participants who do not execute their training will not be allowed to continue with the study.

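### The routine care section attaches log-in, motivation and removal-for-not-training rules to an arm that has no sessions; the arm they cover must be stated and the removal wording reconciled with intention to treat

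*Protocol article*

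**What the plan says.** - **Comparator.** Routine care group: "Participants allocated to the control group will continue to receive routine care according to WHO international practice guidelines". The examples follow: "These activities include engaging in physical education class at school and/or playing with friends at the park or in the backyard". Explanation for the choice of comparators {6b} likewise names routine care and nothing else.
- **Monitoring, in the same Routine care group paragraph.** To secure adherence to the intervention, the team will follow engagement, "reaching out to participants who are not logging in twice per week to understand the reasons for non-compliance and to provide motivation to continue".
- **Removal, in the same paragraph.** "Participants who do not execute their training will not be allowed to continue with the study". No threshold is given and no arm is named.
- **Exercise arm.** Exercise group: "Participants are required to log in and complete the exercises 2 times per week". This is the only section that defines platform sessions.
- **General rule.** Intervention descriptions {11a} describes both arms, sets out contact for those engaging less than twice a week, and then says: "If the participants do not perform 70% of the training (or 17 out of 24 sessions), they will not be allowed to continue participation". Again no arm is named.
- **Analysis.** Statistical methods {20a}: "The study will adhere to the intention-to-treat principle", with baseline observation carried forward for missing data.

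**The concern.** A control child has no platform session to log in to and no training to carry out. Yet the section that defines the control condition tells staff to chase missing log-ins and to stop those who do not train. A reader who applies that section as written has two options, and neither is routine care with full follow-up: prompt control families about a programme they were not assigned, or take control children out of the study.

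Two things are at stake. The first is the contrast: the comparator is meant to be routine care alone, and contact and motivation from the study team is not part of it. The second is follow-up: a child who may not continue has no later accelerometer record, so the primary outcome for that child would have to be imputed. The second issue is not confined to controls, since {11a} words removal for participants in general.

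**Working it through.** **1. The plan's own figure.** Inputs: 2 sessions per week (Exercise group) and 12 weeks (Intervention descriptions {11a}).
- Sessions: 2 × 12 = 24.
- Threshold: 0.70 × 24 = 16.8, rounded up to 17; 17/24 = 70.8%.

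The stated 17 of 24 reproduces. The denominator of 24 comes from the exercise programme only.

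**2. Does the figure carry over to controls?** The protocol assigns controls no sessions, so they have no denominator. Scoring a control as 0 of 24 borrows the other arm's 24. The sound conclusion is that the rule cannot be assessed in this arm; it is not that every control fails it.

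**3. The sections side by side.**

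| Section | Arm named | Content |
|---|---|---|
| Choice of comparators {6b} | Control | Routine care only |
| Intervention descriptions {11a} | None, after describing both | Contact below 2 per week; removal below 17 of 24 |
| Exercise group | Exercise | Log-in and sessions, 2 per week |
| Routine care group | Control, by heading | Routine activity; then log-in contact, motivation and removal |
| Fig. 1 caption | Both | Both groups enter the 12-week follow-up |

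The first, third and fifth rows fit together. The fourth contradicts the first within the section that defines the control condition, and the second does not settle it. The two removal sentences also differ: {11a} has a numerical threshold and speaks of participation, while the routine care section has no threshold and speaks of the study.

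**4. When removal could act.** A child can miss 24 − 17 = 7 sessions and still meet the threshold; the eighth miss makes it unreachable. At 2 per week that could happen after 8/2 = 4 weeks, before T1 at week 12. The protocol does not say when the rule is applied, so this is the earliest possibility and not the stated timing.

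**5. What each outcome does to the analysis.**
- *Contact with controls.* The children are still analysed as randomised, so intention to treat holds. The contrast may be diluted, by an amount the protocol gives no means to estimate.
- *Removal before T1, in either arm.* T1 and T2 are missing. Under baseline observation carried forward, imputed change = baseline − baseline = 0. The child can still be counted in the assigned arm, but with an imputed value. {20a} allows dropouts to be included without requiring it.

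The tension with intention to treat therefore lies in the removal wording, and it applies to both arms.

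**The case against.** The strongest reply is that these are exercise-arm sentences under the wrong heading. They speak of adherence to the intervention, of logging in and of training, all of which exist only in the exercise group. Intervention descriptions {11a} and the Fig. 1 caption carry the routine care group through 12 weeks and then into follow-up, which could not happen if controls were expelled. That reply is probably right about the origin of the text, and it disposes of three stronger readings that a reader might infer:

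- **That every control is removed.** This needs a denominator of 24 that controls are never given, and it contradicts Fig. 1.
- **That controls are urged to be more active, which cuts the 5-minute target difference in daily MVPA.** The text speaks of missed log-ins and motivation to continue; it does not say controls are urged to exercise. Any number of minutes lost would be pure assumption.
- **That intention to treat is broken whichever way the text is read.** Contact does not break it. Removal does not do so automatically either, since {20a} allows dropouts to be analysed and imputes their missing values.

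What the reply does not do is correct the text. That the sentences are misplaced is an inference; the protocol does not say so, and {11a}, where the arm could have been named, is just as open. Nor is this a detail left to a fuller document: it is a positive statement that conflicts with the definition of the comparator.

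**Conclusion.** The contradiction stands. The routine care section states monitoring, motivation and removal rules that cannot belong to an arm without sessions, and no other section limits them to the exercise group. The likely cause is misplaced text, so this is a wording error in the definition of the comparator and not evidence of how controls are in fact handled.

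Its reach is one of two arms, 40 children by Fig. 1 or 42 by the sample size section. No bias, loss of power or number of removed children is claimed. The conclusion rests on one assumption, which the protocol supports throughout: controls are given no platform sessions. A related point stands for both arms: removal for low adherence, as worded, has to be squared with the intention-to-treat statement.

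**What to change.** 1. Reconcile {6b}, {11a}, Exercise group and Routine care group. Take the log-in, motivation and training sentences out of the routine care section, state which arm they cover, and state that controls have no log-in or training condition.
2. Reconcile the removal wording in {11a} and Routine care group with {20a}. State that all randomised children in both arms, whatever number of sessions they complete, are invited to the T1 and T2 assessments with the same reminders and are analysed in their assigned arm.

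The second step must cover both arms. Limiting removal to the exercise group while guaranteeing assessment only for controls would write one-sided removal after randomisation into the plan. Whether and when a child stops the exercise sessions is for the trial team; the request here concerns only assessment and analysis.

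The cost is a small wording amendment, with the ethics approval that the protocol already requires for amendments. It needs no added participants, and T1 and T2 are already planned for both groups.
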